#### Safety evaluation

2.5.3

Any adverse events or abnormalities will be recorded on case report forms no matter what intervention is used. The severity of such adverse events will be described as mild, moderate, or severe, and the relation of the events to the intervention will be evaluated as not related, possibly related, or related. If any serious adverse events occur as the result of a certain intervention, that intervention will be stopped immediately and appropriate corrective action will be taken. Any serious adverse events will be reported promptly to the institutional review board, according to the protocol.

### Sample size calculation

2.6

Using the frequency of onset as the primary outcome measurement, NQuery Advisor software (version 4.0, Statistical Solutions, Ireland) was used to calculate the appropriate sample size. Based on literature research, the sample size was estimated according to the calculation formula of non-inferiority test. α = 0.025, β = 0.2, non-inferiority margin δ = 15%, ε is the actual difference among groups. One-way test was performed, and the sample size was calculated to show that 103 samples are needed in this study. One hundred eighteen cases were needed in the 3 groups, assuming a 10% non-adherence to treatment and a 5% loss to follow-up. In this study, a total of 120 cases were selected from 3 groups, 40 cases in each group.

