## Introduction

1

Chemotherapy-induced nausea and vomiting (CINV) is among the most common and distressing side effects of chemotherapy.^[1]^ It has been shown to significantly affect the quality of life (QoL) and daily function of patients receiving chemotherapy.^[2]^ Moreover, CINV, as a prognostic factor for overall survival, is so severe in some cases that it interrupts the treatment of primary cancer and increases the risk of disease progression,^[3,4]^ which result in treatment-outcome reduction.^[5]^

Cisplatin, which is a cornerstone of chemotherapy for the treatment of multiple cancers, is a highly emetogenic chemotherapy drug.^[6]^ Over 90% cancer patients will vomit within the first 24 hours after the administration of cisplatin-based chemotherapy unless antiemetic drugs are used.^[7]^ Even with the guideline-recommended antiemetic drugs, cisplatin-induced vomiting is controlled in only 60% of patients; therefore, considerable numbers of patients still experience nausea.^[8]^

Although the mechanisms underlying CINV are not clear enough,^[9]^ to date, commonly prescribed medicines,^[10]^ for nausea and vomiting are: 5-hydroxytryptamine-3 serotonin receptor antagonists (5-HT3RA), Neurokinin1 receptor antagonists (NK-1RA), and corticosteroid.^[11]^ However, for all its prominence in CINV management, these drugs are subject to considerably economic burden and side effects, namely insomnia, headaches, dizziness, and constipation.^[12]^ Thus, additional treatments are urgently needed to effectively manage and ameliorate chemotherapy-induced nausea and vomiting (CINV), without those defects in the wake of antiemetic drugs.

An increasing body of evidence points that electroacupuncture (EA) may provide modest benefits in the treatment of CINV.^[13]^ However, the spread of it is surprisingly slow, and EA is still judged as a highly suggestive but not conclusive treatment.^[14–17]^ For certain patients, they are reluctant to accept EA treatment for their intolerance to needling. The problems and limits of EA center on how it manipulate. Thus, auricular acupuncture (AA) might be a sound treatment to feather all patients’ needs for convenience and comfort. Compared with a pile of studies conducted the access to the effectiveness of EA against CINV, the role of AA has received less attention,^[18]^ and the literatures on AA are limited in number with uncertain quality.

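### With no true difference between arms, the stated sample size gives the claimed 80% non-inferiority power only at an event rate near 5% or 95%

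*Protocol article*

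**What the plan says.** Section 2.6 (Sample size calculation) takes a binary onset measure as the sizing endpoint ("Using the frequency of onset as the primary outcome measurement") and a non-inferiority framework: "the sample size was estimated according to the calculation formula of non-inferiority test". The design parameters are "α = 0.025, β = 0.2, non-inferiority margin δ = 15%, ε is the actual difference among groups". The symbol ε is defined but given no value. The section adds "One-way test was performed", read here as one-sided, and then "the sample size was calculated to show that 103 samples are needed in this study". Inflation follows: "One hundred eighteen cases were needed in the 3 groups, assuming a 10% non-adherence to treatment and a 5% loss to follow-up". The final size is "a total of 120 cases were selected from 3 groups, 40 cases in each group".

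The section does not give the assumed event rate, does not say whether onset means nausea, vomiting or either, and does not name the two arms being compared. Section 2.4 gives guideline antiemetics to every arm. For that setting the Introduction quotes one rate: "cisplatin-induced vomiting is controlled in only 60% of patients".

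**The concern.** A non-inferiority sample size for proportions depends strongly on the event rate and on the true difference. For a 15-point margin, about 34 per arm is very small unless the event is very rare or almost universal. The only rate the article quotes under guideline antiemetics is neither.

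Comparing auricular acupuncture (AA) with electroacupuncture (EA) is the stated aim. If power is well below 80%, a failure to show non-inferiority would be a likely result even with two equally effective treatments. A reader who trusted the 80% claim could take that failure as evidence that one treatment is worse.

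**Working it through.** **Inputs.** From Section 2.6: one-sided α = 0.025 (z = 1.960), β = 0.2 (z = 0.842), margin 0.15 taken as an absolute difference, 103 before inflation, 118 after, 120 enrolled as 40 per arm. From the Introduction: 60% vomiting control, so about 40% with vomiting. Assumed: ε = 0 unless stated, because the section gives no value.

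**Reproducing the plan's figures.** 103 × 1.15 = 118.45, which gives the stated 118. As 118 is said to cover three groups, 103 is also a three-arm total: 103/3 = 34.3 per arm. The 103 itself cannot be reproduced, because neither the event rate nor ε is given.

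**Event rate implied by 103.** With equal true rates p,

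n per arm = (1.960 + 0.842)² × 2p(1−p) / 0.15².

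Setting n = 34.3 gives p(1−p) = 0.049, so p is about 5% (or 95%). Setting n = 40 gives p(1−p) = 0.057, so p is about 6% (or 94%).

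**Required size and power at other rates.** Power = Φ(0.15/√(2p(1−p)/n) − 1.960).

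| Event rate, both arms | n per arm for 80% | Power, 34 per arm | Power, 40 per arm |
|---|---|---|---|
| 5% | 34 | 81% | 87% |
| 10% | 63 | 54% | 61% |
| 20% | 112 | 34% | 39% |
| 30% | 147 | 27% | 31% |
| 40% | 168 | 24% | 28% |
| 50% | 175 | 24% | 27% |

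The formula is symmetric about 50%, so across all common rates from 10% to 90% power is at most 54% (34 per arm) or 61% (40 per arm).

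Worked example at 40%, 40 per arm: standard error √(0.48/40) = 0.1095; 0.15/0.1095 − 1.960 = −0.59; Φ(−0.59) = 0.28. A simulated Wald test at this rate gives 26.8% (34 per arm) and 28.7% (40 per arm), close to the formula.

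**What ε would be needed.** With a 40% event rate in the reference arm, 40 per arm reaches 80% if the tested arm is truly about 14 points better. With 34 per arm, power is 79% at 16 points and 82% at 17. If the tested arm is truly 5 points worse, power is 13% (34 per arm) to 15% (40 per arm).

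**Other readings.** A one-sided α of 0.05 still needs 132 per arm at 40% with ε = 0. If 103 were per arm it would fit an 18% event rate with ε = 0, but the statement that 118 covers the three groups rules this out.

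**Precision at 40%.** 95% interval half-width: 1.96 × √(0.48/40) = 0.215, and 1.96 × √(0.48/34) = 0.233. So about ±21 to ±23 points, wider than the 15-point margin.

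**Inflation.** Allowing for 15% attrition requires division: 103/0.85 = 121.2, so 122; treating the two losses separately, 103/(0.90 × 0.95) = 120.5, so 121. The plan has 118.

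**The case against.** The strongest reply is that the planning inputs are not visible. The article condenses a fuller document and refers to literature for its assumptions. The 60% figure is a background sentence, covers vomiting only, and describes antiemetics alone; if AA is compared with EA, both arms also receive acupuncture and the rate could be lower. If the formula was run for acupuncture against control, a favourable ε would be an ordinary input, and about 14 to 17 points would justify the size.

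This stands to the extent that a reader might infer from the table that the trial's actual power is 24–28%. The document does not support that: the figure holds only for a 40% event rate and ε = 0, and Section 2.6 fixes neither. Nor is it shown that 103 was wrongly computed from whatever inputs were used. The reply does not rescue the 80% claim as printed, which with ε = 0 fails at every common rate from 10% to 90%; no offsetting advantage is stated.

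Two other strong readings also go too far. Failure to show non-inferiority would not be near-certain: at 40% with equal arms it is 72–76%. And one might say that 120 × 0.85 = 102 leaves too few evaluable patients. But Section 2.8 analyses by intent to treat, so non-adherent patients stay in and only the 5% loss removes data: 120 × 0.95 = 114, above 103.

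**Conclusion.** The 80% power statement is unsupported as written. Taking 103 as the three-arm total, a 15-point absolute margin, one-sided 0.025 and ε = 0, it holds only near a 5% or 95% event rate. At the one rate quoted for patients on guideline antiemetics (about 40% vomiting, not stated to be the planning rate), power would be about 24% with 34 per arm and 28% with 40 per arm, against 168 per arm needed. Reaching 80% at that rate would require a true advantage of about 14 points (40 per arm) to 16–17 points (34 per arm), which is not stated. The power claim needs correction because it is part of the only justification given for the trial's size. The inflation slip is real but minor.

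**What to change.** Keep 120 patients and revise Section 2.6:

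- State the reference event rate, what counts as onset, the value of ε, and which pair of arms the non-inferiority test compares.
- Replace the 80% claim with power recomputed from those inputs at the expected evaluable number. With ε = 0 this is about 24–28% at 40% incidence and 34–39% at 20% (34 to 40 per arm).
- Report the expected 95% interval half-width for AA versus EA, about ±21 to ±23 points at 40% incidence, and say that failure to show non-inferiority will not be read as evidence that AA is inferior. This does not require dropping the non-inferiority hypothesis.
- Correct 118 to 122 (or 121 if 0.90 × 0.95 is used), noting that non-adherent patients remain in the intent-to-treat analysis, so little follows from it in practice.

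The cost is rewording in one section and a less favourable stated power. No extra patients are needed.

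### Section 2.6 reaches 118 by multiplying 103 up by 15%; dividing the allowance out gives 122 (121 if the losses are sequential), with almost no practical effect at the planned 120

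*Protocol article*

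**What the plan says.** Section 2.6 (Sample size calculation) of the protocol article gives three figures in sequence.

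- The requirement before any allowance: "the sample size was calculated to show that 103 samples are needed in this study".
- The figure after the allowance: "One hundred eighteen cases were needed in the 3 groups, assuming a 10% non-adherence to treatment and a 5% loss to follow-up".
- The enrolment plan: "a total of 120 cases were selected from 3 groups, 40 cases in each group".

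The section does not show the step from 103 to 118. Section 2.8 (Statistical analysis) places every efficacy and safety analysis on the intent-to-treat population.

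**The concern.** An allowance for attrition is a fraction of the patients enrolled. If a fraction d of those enrolled will not count, the number to enrol is the requirement divided by (1 − d). Multiplying the requirement by (1 + d) gives too small a number, and the 118 looks as if it came from that shortcut.

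The input, the two rates and the output are all printed, so any reader can check the step by hand. What is at stake is whether section 2.6 is right in presenting 118, and by extension 120, as enough to retain 103 after the losses it assumes. There is a second question: whether patients who do not adhere should be counted as lost at all, given the analysis set in section 2.8.

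**Working it through.** **Inputs, all from section 2.6 unless noted**

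- Requirement before the allowance: 103 in total, taken as given.
- Non-adherence 10%; loss to follow-up 5%; together 15%.
- Figure after the allowance: 118. Planned enrolment: 120, 40 per group.
- One-sided α = 0.025 and β = 0.2 (power 80%), reading "One-way test was performed" as one-sided.
- Analysis set: intent-to-treat (section 2.8).

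**Step 1. Reproduce the stated 118**

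- Multiply up, rates pooled: 103 × 1.15 = 118.45. Rounded down, this is 118.
- Multiply up, rates in turn: 103 × 1.10 × 1.05 = 118.97, which would be 118 only if truncated.
- Divide out, pooled or sequential (step 2): 121.2 or 120.5.

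Only the multiply-up forms land on 118 to 119. The pooled form is the natural source. Required sample sizes are rounded up, so even that form would give 119.

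**Step 2. Divide the allowance out**

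- Pooled: 103 / (1 − 0.15) = 103 / 0.85 = 121.2, so 122.
- Sequential: 103 / (0.90 × 0.95) = 103 / 0.855 = 120.5, so 121.
- Three equal groups: 3 × 41 = 123 on either reading.

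The stated 118 is 122 − 118 = 4 too low, or 121 − 118 = 3 too low.

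**Step 3. Reverse check, counting non-adherent patients as lost**

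| Enrolled | Pooled (× 0.85) | Sequential (× 0.855) | Against 103 |
|---|---|---|---|
| 118 | 100.3 | 100.9 | short |
| 120 | 102.0 (34 per group) | 102.6 | short by about 1 |
| 121 | – | 103.5 | met |
| 122 | 103.7 | – | met |

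**Step 4. Cost in power at 120**

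If 103 gives exactly 80% power at one-sided 0.025, the standardised effect is 1.960 + 0.842 = 2.802. With 102 it becomes 2.802 × √(102/103) = 2.788. Power is Φ(2.788 − 1.960) = Φ(0.828), about 79.6%. The loss is about 0.4 percentage points.

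**Step 5. Intent-to-treat headcount**

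Non-adherent patients stay in this set, so only the 5% loss to follow-up removes anyone: 120 × 0.95 = 114, and 118 × 0.95 = 112.1. Both exceed 103.

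**The case against.** The strongest reply is that nothing of consequence follows. The trial enrols 120, not 118. Under the intent-to-treat analysis of section 2.8, 120 leaves 114 with follow-up, comfortably above 103. Even if non-adherent patients are counted as lost, the gap is about one patient. The base of 103 cannot be checked either, because section 2.6 names ε without a value and gives no event rate, so precision to one patient means little.

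Most of that stands, and it rules out two stronger readings that a reader might infer.

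- **That the planned enrolment fails to deliver the required sample.** This holds only if the 10% who do not adhere are removed from the analysis. Section 2.8 keeps them in, so the documents do not support a headcount shortfall for the planned analysis.
- **That the shortfall is as large as five patients.** That figure comes from setting 118 against 105 (35 in each of three groups). But 118 is an intermediate figure and not the enrolment target, and the protocol nowhere states a requirement of 105.

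The reply does not rescue the sentence itself. Section 2.6 combines both rates to produce 118, and on those terms the figure is wrong. Nor does the intent-to-treat argument make the inflation right. If non-adherent patients stay in, they are not patients to be replaced. Their effect is to dilute the contrast between groups, and adding patients in proportion to a headcount loss is not a calculation of that effect. The size of the dilution has not been quantified here.

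**Conclusion.** The point holds as a minor arithmetic correction. On the protocol's own 10% and 5%, the figure after the allowance should be 122 (121 if the losses are sequential; 123 for three equal groups), and not 118. The planned 120 leaves about 102 patients who are adherent and followed up, one short of 103, with a negligible effect on power. It leaves about 114 followed up in the intent-to-treat set, where there is no headcount shortfall.

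This rests on taking 103 as a correct total across the three groups and on reading both rates as fractions of those enrolled. It does not show that the trial is too small. Whether 103 is itself adequate is a separate question that this arithmetic cannot settle.

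**What to change.** In section 2.6:

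1. Replace 118 with 122, showing 103/0.85 (or with 121, showing 103/(0.90 × 0.95), if the losses are meant to act in sequence).
2. Keep 120 enrolled, 40 per group, and say what it yields: about 102 patients who are adherent and followed up (34 per group), and about 114 followed up in the intent-to-treat set.
3. Add a clause saying that in the intent-to-treat analysis the 10% non-adherence acts as dilution of the contrast, which the inflation does not cover.

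The cost is a sentence or two of text. No extra patients are needed and no analysis changes. The text would simply no longer imply that 120 retains 103 after both losses.

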### Randomization and blinding

2.7

Randomization of subjects to 2 groups will be on the basis of a concealed allocation approach using statistical analysis PROCPLAN statements (SAS 9.4; World Headquarters SAS Institute Inc., Cary, NC). A computer-generated list of random numbers will be used to determine the allocation of the participants, with numbered opaque sealed envelopes containing the randomization schedule. The envelopes will be kept by an investigator who is not an assessor in the study and will be informed of the outcomes at the end of the study. In this trial, participants and acupuncture practitioners cannot be blinded. The researchers recording the outcomes and those making the conclusions will be all blinded to patients’ assessments.

### Statistical analysis

2.8

All continuous data will be expressed as mean ± standard deviation. For these data, a *t* test will be applied to compare normally distributed data between the 2 groups, while the Wilcoxon rank sum test applied for non-normally distributed data. Categorical variables will be presented as frequency and percentage and analyzed using the chi square (χ2) test or the Mann–Whitney *U* test where appropriate. Values of *P* < .05 (2-tailed) will be considered statistically significant. All the efficacy and safety analyses will be performed using the intent-to-treat population. All statistical analyses will be performed using the Statistical Package for the Social Sciences (version 13.0; SPSS; Chicago, IL). A third person performed blinded estimation and statistics of the curative effect.

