### Population

2.3

All participants will be recruited from the Oncology Department of Chengdu Second People's Hospital, a tertiary hospital, which plays the leading role at the local. We will recruit cases diagnosed with magnificent tumor confirmed by clinicopathology or cytology undergoing the cisplatin-based chemotherapy regimens. Participants who fulfil the inclusion criteria and sign informed consent forms will enter the screening period, otherwise will be excluded before randomization. Chengdu is the largest base of industrial technology and commercial and financial center in the west of China, with a population of 14,047,600, where could collect more cases of diversity. The duration of enrollment is from December 31, 2020 to December 30, 2022.

Eligible participants are all adults aged 18 to 75 years, diagnosed with magnificent tumor confirmed by clinicopathology or cytology undergoing the cisplatin-based chemotherapy regimens and an expected survival time of >3 months. They are still in relatively good physical condition, with a Kamofsky score >60.

The exclusion criteria are as follows: nausea and vomiting caused by intracranial or other metastases, severe gastrointestinal obstruction, or combine organic disorders; recent using drugs may cause nausea and vomiting; participants with allergy history, especially to metal and tape; participants with inability to communicate; participants participating in another clinical trial within 3 months.

The withdrawal criteria are as follows: terminate or adjust the chemotherapy regimen after evaluation by oncologists due to clinical exacerbation; at the patient's own request or at the request of their legal representative.

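### Section 2.8 fixes unadjusted tests and uses neither the strata nor the baseline values already held, which costs a modest amount of precision but not validity

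*Protocol article*

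**What the plan says.** Section 2.8 (Statistical analysis) sets the method for each type of variable. For continuous data, "a *t* test will be applied to compare normally distributed data between the 2 groups", with a rank sum test where normality fails. For the rest, "Categorical variables will be presented as frequency and percentage and analyzed using the chi square" or the Mann–Whitney test. The decision rule is "Values of *P* < .05 (2-tailed) will be considered statistically significant". The section mentions no model, covariate, stratified test or confidence interval.

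Section 2.3 (Population) makes two baseline values part of eligibility: "Eligible participants are all adults aged 18 to 75 years", and "They are still in relatively good physical condition, with a Kamofsky score >60". It also requires a cisplatin-based regimen, names no tumour site, and places exclusion of ineligible patients before randomisation.

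Section 2.6 (Sample size calculation) uses frequency of onset as the endpoint, with a one-sided α of 0.025 and a "non-inferiority margin δ = 15" per cent. It ends with "a total of 120 cases were selected from 3 groups, 40 cases in each group".

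Section 2.7 (Randomization and blinding) describes a computer-generated list and sealed envelopes, and mentions no strata. The Discussion says that stratified block randomisation will be applied to reduce bias, but does not name the factors.

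**The concern.** Patients of any adult age up to 75, with any malignant tumour and any Karnofsky score above 60, are split into arms of 40. If age or performance status is related to nausea and vomiting, an unadjusted comparison leaves that variation in the error term. In a trial where the arms happen to differ on such a factor, the estimate is also displaced. Both values are in hand for every patient, so using them needs no new data.

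The Discussion adds to the point. If the randomisation is stratified, someone has judged certain factors worth balancing. An analysis that ignores them gives up some of the precision that stratification was meant to buy.

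At stake is the width of the interval for the difference between auricular acupuncture (AA) and electroacupuncture (EA), the comparison named as the study's aim. Section 2.6 sets a 15-point margin for a non-inferiority question, although it does not say which pair of arms the margin applies to.

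**Working it through.** **The plan's own figures.** The article gives no figure for the effect of adjustment. Its sample size is 103 before losses and 118 after; 103 × 1.15 = 118.45, so 118 comes from multiplying by 1.15. The 103 cannot be reproduced, because neither an event rate nor a value for ε is given. With no true difference, n per arm = 2p(1 − p)(1.96 + 0.84)² / 0.15². A total of 103 over three arms then fits a rate of about 5%, whereas a 40% rate needs 168 per arm.

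**Inputs.** From the document: 40 per arm, a margin of 15 points, one-sided α of 0.025. Assumed, because the document does not give them: a 40% event rate, and a baseline factor present in half the patients that separates risk by D = 20, 30 or 40 points. D = 0 is also possible.

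**Step 1: how much imbalance chance leaves.** Under simple randomisation, the difference between two arms in the prevalence of a 50% factor has SD √(2 × 0.25/40) = 11 points. The exact binomial probability of a difference of 15 points or more is 0.219 for one pair of arms. For any factor that is stratified in blocks, the probability is smaller.

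**Step 2: what adjustment gains.** R² = (D/2)² / (0.40 × 0.60). Equivalent n = 40/(1 − R²), ignoring the small cost of estimating the covariate effects. The shift from a 15-point imbalance is 0.15 × D. The 95% half-width is 1.96 × √(0.48/n).

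| D | R² | Equivalent n per arm | Shift at 15-point imbalance | 95% half-width |
|---|---|---|---|---|
| 0 (or no adjustment) | 0 | 40.0 | 0 if D = 0 | 21.5 points |
| 20 points | 0.042 | 41.7 | 3.0 points | 21.0 points |
| 30 points | 0.094 | 44.1 | 4.5 points | 20.5 points |
| 40 points | 0.167 | 48.0 | 6.0 points | 19.6 points |

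**Step 3: validity and power by simulation.** Settings: 40 per arm, a binary outcome, three covariates, linear adjustment, 5,000 runs per setting. With no treatment effect, the unadjusted test rejected in 0.045 to 0.058 of runs in every setting. With one fixed treatment effect (−1.35 on the log-odds scale) and simple randomisation, power was:

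| R² | Unadjusted | Adjusted |
|---|---|---|
| 0 | 0.73 | 0.71 |
| about 0.04 | 0.70 | 0.71 |
| about 0.14 | 0.63 | 0.69 |

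Stratified blocks on one factor gave nearly the same figures.

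**Step 4: against the margin.** At a 40% rate the unadjusted standard error is √(2 × 0.24/40) = 11 points. With an observed difference of zero, the interval clears a 15-point margin only if 1.96 × √(0.012 × (1 − R²)) < 0.15. That needs 1 − R² < 0.0059/0.012 = 0.49, so R² above about 0.51. Non-inferiority power with no true difference is about 28% unadjusted and about 33% at R² = 0.20.

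**The case against.** The strongest reply is that nothing here is wrong. Randomisation makes the unadjusted tests valid, and their standard error already allows for chance imbalance: a shift of 3 to 6 points is only 0.27 to 0.55 of the 11-point standard error. That stands. A reader might infer from the imbalance figures that the planned comparison is biased or rejects too often. The document does not support this, and the simulation shows type I error at about 5%.

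A reader might also take 22% as the chance of a 15-point imbalance in this trial. That figure assumes simple randomisation. The Discussion promises stratified blocks, so the figure overstates the imbalance for any factor that is stratified, and the article does not say which factors those are.

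Third, no passage says that age or Karnofsky score predicts nausea and vomiting in these patients. Performance status is restricted to scores above 60, and everyone receives cisplatin. The prognostic strength is an assumption, and a null value, where adjustment loses slightly, belongs in the range. Regimen has no defined levels, so it cannot simply be added to a model.

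Last, adjustment may sit in an analysis plan that is not shown. That would not remove the point, because section 2.8 states the tests rather than leaving them open. If such a plan adjusts, the two texts need aligning.

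**Conclusion.** The point holds as a modest loss of precision from a stated choice of method. Section 2.8 uses neither the strata that the Discussion promises nor two baseline values collected for every patient. Under the assumed 40% rate and a factor held by half the patients, an R-squared of 0.04 to 0.17 would make 40 per arm worth about 42 to 48. At an R-squared of 0 there is no gain and possibly a small loss.

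It would be tempting to say that adjustment decides whether the 15-point margin is met. It does not: over the assumed range the half-width goes from 21.5 to 19.6 points, so an observed difference of zero fails either way. The small sample is a separate and larger problem.

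The change is still worth making. It costs almost nothing, and the model supplies a risk difference with an interval, which the margin in section 2.6 requires and the two-tailed tests in section 2.8 do not provide.

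**What to change.** In section 2.8, pre-specify the primary AA–EA comparison on the onset endpoint of section 2.6 as follows:

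- Fit a logistic model with arm, the stratification factors actually used (named in the protocol), age and Karnofsky score. Include regimen only if it is reduced in advance to two levels.
- Standardise the fitted model to a risk difference, with a two-sided 95% interval read against the 15% margin. This matches the one-sided α of 0.025 in section 2.6.
- Keep the unadjusted difference and its interval as a sensitivity analysis.
- Fix the covariates and their coding before any outcome data are seen.

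The cost is wording and slightly more analysis work; no new patients or baseline measurements are needed. Events per parameter will be few. At a 40% rate the two arms give 0.40 × 80 = 32 events. Arm, age, Karnofsky score and one two-level factor make four terms besides the intercept, or 8 events each, so the list should stay short. If the covariates turn out to be weakly prognostic, there will be little or no gain.

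### The trial is sized for non-inferiority with a 15% margin, but the stated analysis contains only tests of no difference, so the margin is never used and non-inferiority cannot be shown

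*Protocol article*

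**What the plan says.** Section 2.6 (Sample size calculation) states that "the sample size was estimated according to the calculation formula of non-inferiority test". Its inputs are "α = 0.025, β = 0.2, non-inferiority margin δ = 15%, ε is the actual difference among groups", and the test is one-sided: "One-way test was performed, and the sample size was calculated to show that 103 samples are needed in this study". The endpoint used for sizing is the frequency of onset. No event rate and no value of ε is given, and no test arm or reference arm is named. The planned size is 120, with 40 per arm.

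Section 2.8 (Statistical analysis) gives the t test or the Wilcoxon rank sum test for continuous data and the chi-square or Mann–Whitney test for categorical data. Results are judged at P < .05, and the text goes on "2-tailed) will be considered statistically significant. All the efficacy and safety analyses will be performed using the intent-to-treat population". The section contains no margin, no confidence interval and no non-inferiority criterion.

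The aim, in the Abstract, Introduction and Discussion, is to compare AA with EA. Non-inferiority is mentioned only in Section 2.6.

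**The concern.** A sample size calculation and an analysis should address the same hypothesis. Section 2.6 asks whether one arm is worse than another by less than 15 points. Section 2.8 asks whether two arms differ at all. Rejecting the second null does not establish non-inferiority, and failing to reject it does not either.

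The main AA–EA conclusion is at stake. With 40 per arm, a non-significant P value is likely even when one treatment is worse by the whole margin. Without a margin rule in the plan, such a result could be reported as the two treatments being alike. If the hypothesis were chosen after the data had been seen, the error rate set in Section 2.6 would no longer apply.

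**Working it through.** **1. The two sections side by side**

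| | Section 2.6 | Section 2.8 |
|---|---|---|
| Null hypothesis | worse by 15 points or more | no difference |
| Margin | 15% | not mentioned |
| Error level | 0.025, one-sided | 0.05, two-sided |
| Decision rule | non-inferiority formula | P < .05 |

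The error levels agree: a two-sided 95% confidence interval leaves 2.5% in each tail. The null hypothesis and the use of the margin do not agree.

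**2. The plan's own figure.** The 103 cannot be verified, because Section 2.6 gives neither the event rate nor ε. With ε = 0 and common rate p, the usual formula per arm is

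n = 2p(1−p)(1.960 + 0.842)² / 0.15² = 348.8 × 2p(1−p).

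- p = 5%: 33.1, so 34 per arm and 102 over three arms, close to 103.
- p = 10%: 63 per arm.
- p = 20%: 112 per arm.
- p = 30%: 147 per arm.
- p = 40%: 168 per arm.
- p = 50%: 175 per arm.

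**3. What the stated test does when the deficit equals the margin.** Assumptions, none stated in the protocol: AA versus EA is the pair, the endpoint is CINV incidence, EA incidence is 20%, 30% or 40%, and AA incidence is 15 points higher. The nearest figure in the text is the Introduction's 60% control of vomiting under guideline drugs, which is neither an EA rate nor a stated design input.

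Normal approximation for 30% versus 45% at 40 per arm:

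- Pooled rate 0.375; standard error under the null √(2 × 0.375 × 0.625 / 40) = 0.108.
- Difference needed for significance: 1.96 × 0.1083 = 0.212.
- Standard error under the true rates √((0.45 × 0.55 + 0.30 × 0.70) / 40) = 0.107.
- P(non-significant) ≈ Φ((0.212 − 0.150) / 0.107) ≈ 0.72.

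Exact binomial enumeration, uncorrected chi-square, 40 per arm:

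| EA / AA incidence | chi-square non-significant | upper 95% Wald limit below 15 points |
|---|---|---|
| 20% / 35% | 67.8% | 2.6% |
| 30% / 45% | 71.5% | 2.5% |
| 40% / 55% | 71.2% | 2.8% |

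Newcombe limits also pass in under 3% of trials in these settings. At 34 per arm, about 103/3, chi-square is non-significant in 70–78% and the margin rule passes in about 2.5–3%.

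**4. One data set.** CINV in 24/40 on AA and 20/40 on EA: difference +10 points, P = 0.37, 95% Wald interval −11.7 to +31.7 points. Section 2.8 reports no significant difference, yet the interval includes deficits of twice the margin.

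**5. Power of a margin-based rule at 40 per arm.** With no true difference, the chance that the upper Newcombe limit is below 15 points is about 54% (common rate 10%), 40% (20%), 33% (30%) and 29% (40–50%).

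**The case against.** Several points on the other side are sound.

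- **Reading of P > .05.** A reader might infer that the plan will treat a non-significant result as AA being as good as EA. The protocol states no such rule; Section 2.8 says only when a result counts as significant. This is a risk, and the 68–71.5% does harm only if the result is read that way.
- **The pair.** AA versus EA is inferred from the stated aim. Section 2.6 speaks only of a difference among groups.
- **Two-tailed testing.** A reader might see a clash between one-sided 0.025 and two-sided 0.05. There is none.
- **Analysis set.** A reader might call intent-to-treat alone an error for non-inferiority. It is a legitimate primary set, and a supporting per-protocol analysis may sit in a fuller document. Non-adherence can pull arms together, but this depends on who stops and on their outcomes. If 10% in both arms are non-adherent and share one event rate, 15 points shrinks to 0.9 × 15 = 13.5.
- **Which section is wrong.** The aim and the tests fit a trial of difference, so the formula in Section 2.6 may be the misplaced part.

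An analysis plan that is not shown does not remove the conflict. Section 2.8 itself fixes the tests and the significance rule, and they answer a different question from Section 2.6. The mismatch stands whichever section is in error.

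**Conclusion.** The concern holds as a contradiction between Sections 2.6 and 2.8, and it must be resolved before the data are analysed. Followed as written, the analysis cannot test the hypothesis for which the trial was sized, because the 15% margin is never applied. That conclusion needs no assumption.

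The size of the risk does rest on assumptions: the AA–EA pair, CINV incidence as the endpoint, and EA incidence of 20–40%. Under these, a P value above .05 at 40 per arm is close to uninformative about a 15-point deficit.

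The documents do not support saying that the plan commits to reading non-significance as equivalence, that its two-sided level is wrong, or that the intent-to-treat set is wrong.

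**What to change.** Reconcile the two sections in one of two ways.

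**If non-inferiority is intended**, Section 2.8 should:

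- name the pair, the reference arm and the endpoint;
- conclude non-inferiority of AA to EA only if the upper limit of the two-sided 95% confidence interval (Newcombe or score) for the AA minus EA difference in CINV incidence is below 15 percentage points;
- say that a non-significant P value is not evidence of equivalence;
- keep the two-tailed tests for each acupuncture arm against control.

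A supporting per-protocol analysis is a useful addition, since Section 2.6 expects 10% non-adherence. It is a suggestion and not a condition of the fix.

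**If non-inferiority is not intended**, remove the margin and the non-inferiority formula from Section 2.6 and justify the sample size for a difference between named arms.

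**Cost.** The wording is a few sentences, but the consequences are larger. Under the first option the claim becomes harder to make, and Section 2.6 must state its event rate and ε and restate its power. With no true difference, 40 per arm gives only about 29–54% at assumed common rates of 10–50%, while 80% power needs 63 per arm (10%) to 175 per arm (50%) before any allowance for loss. Changing Section 2.8 alone would leave a trial with limited power to show non-inferiority. Under the second option the sample size section has to be redone.
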